### Statistical analysis

For the main analysis of outcomes, we will use mixed models, with the mother or the pregnancy as the random effect to allow for clustering due to multiple births. Skewed lung-function outcome data will be log-transformed.

All study outcome analyses will be adjusted for observed baseline imbalances between groups by incorporating the unbalanced factors as fixed effects in the multifactorial model. Sensitivity analyses will be conducted to explore the robustness of adjustment for baseline imbalances between groups. Propensity score matching, used in the follow up of UKOS patients when aged 16–19,^44^ will be utilised as part of the sensitivity analysis methodology. Unadjusted and adjusted analyses will be presented to show the effects of adjustment as estimates with 95% confidence intervals. As we have a clearly predefined single primary outcome, FEV_1_/FVC, we will not adjust for multiple testing of the secondary outcomes. Neonatal baseline data will be compared for the children recruited and not recruited at age 24–28 years to determine the representativeness of the group with follow-up data. Those variables that differ between recruited versus not recruited will be further adjusted for a sensitivity analysis. Some participants will be unable to complete all tests and, so, multiple imputation using chained equations will be used to impute missing data.

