## Introduction

Extremely prematurely born infants (<28 weeks gestational age) make up 6% of all preterm admissions to the neonatal unit.^1^ Extremely premature infants can develop significant cardiopulmonary morbidities including chronic lung disease (bronchopulmonary dysplasia [BPD]), pulmonary hypertension (PH), morphological changes in heart structure and reduced exercise tolerance. As a consequence, an estimate of the incremental cost for an extremely preterm child surviving to 18 years is £94,740 as compared to £22,885 for a term survivor.^2^

Chronic respiratory morbidity is more common in infants who had BPD. They have more hospital admissions, more frequent respiratory symptoms requiring treatment and lung function abnormalities that persist into childhood and adolescence compared to those who did not have BPD.^3,4^ Chronic respiratory morbidity, however, can also occur in infants who did not develop BPD. Indeed, in a meta-analysis of the results of 55 cohorts, there was lower forced expiratory volume in 1 s/forced vital capacity (FEV_1_/FVC) in those born prematurely compared to those born at term, irrespective of a history of BPD.^5^

Puberty is the last positive effector of lung function with rapid growth of the airways and lung parenchyma.^6^ Yet studies have demonstrated that prematurely born adolescents may not achieve the same level of lung function during puberty as their term born counterparts.^7^ Indeed, lung function may deteriorate during puberty in those who had BPD,^8,9^ particularly if they received corticosteroids postnatally.^10^ Corticosteroids are administered to prematurely born infants to facilitate early extubation and reduce the incidence of BPD. In the United Kingdom Oscillatory Study (UKOS) cohort, postnatal corticosteroid exposure was shown to be associated with impaired lung function at 11–14 years^10^ and 16–19 years.^11^ Indeed, during that time period the lung function of those exposed to corticosteroids had declined, putting them at risk of the early development of chronic obstructive pulmonary disease (COPD).^10,11^ Given the evidence for chronic respiratory morbidity in childhood and adolescence, whether extremely prematurely born adults who were cared for in the modern era of neonatal intensive care (routinely administered antenatal corticosteroids and postnatal surfactant) are at increased risk of further respiratory morbidities and the premature onset of COPD needs urgently testing.

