## Methods

### Study design

This is a prospective cohort study of adults (aged 24–28 years) born prematurely (before 29 weeks gestation) and term born controls. The study duration will be 24 months, with a one month set up period, 18 months of assessments and five months of analysis and write up. The study aims to recruit 200 individuals: 150 participants from the UKOS cohort and 50 control term born participants.

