**Neonatal**
Male sex
Birthweight (g)
Birthweight (z score)
Gestation at birth (weeks)
Multiple birth (Yes/No; if yes: twin/triplet/quadruplet)
Surfactant administration (yes/No; if yes: number of doses)
Mode of ventilation at birth (Conventional ventilation/High frequency ventilation)
Postnatal glucocorticoids (yes/No; if yes: number of courses)
Oxygen dependence at 36 weeks of post menstrual age (yes/no)
Oxygen dependency at 28 days (yes/no)
Oxygen dependent at discharge (yes/no)

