### Outcome measures

This is a long-term follow up of lung function and cardiac outcomes in a group of extremely prematurely born adults who have had exposure to antenatal steroids and postnatal surfactant.

Our primary outcome is FEV_1_/FVC in extremely prematurely born adults with postnatal corticosteroid exposure versus no postnatal corticosteroid exposure.

Our secondary outcomes will include spirometric lung function, cardiopulmonary exercise test of maximum oxygen uptake (VO_2_) and PAP estimation by cardiac ultrasound of UKOS participants compared to term born controls.

We will also compare these primary and secondary outcomes in participants enrolled in the UKOS trial as per their initial designation of mode of ventilation.

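### Choosing covariates by observed imbalance can drop true confounders of the steroid contrast, and it leaves the door open to post-exposure and post-randomisation adjustment

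*Protocol article*

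**What the plan says.** The primary outcome (protocol article, Outcome measures) is FEV1/FVC "in extremely prematurely born adults with postnatal corticosteroid exposure versus no postnatal corticosteroid exposure". The Study design section describes a cohort study. The randomised factor in UKOS was mode of ventilation (Hypothesis), so steroid exposure was not allocated at random. The ventilation groups are also to be compared, "as per their initial designation of mode of ventilation".

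The Statistical analysis section fixes how covariates are chosen: "All study outcome analyses will be adjusted for observed baseline imbalances between groups by incorporating the unbalanced factors as fixed effects". It names no covariates and no criterion for imbalance, and it does not limit "baseline" to what preceded the exposure. It does promise unadjusted and adjusted estimates with 95% confidence intervals, sensitivity analyses of the adjustment, and propensity score matching among them.

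The neonatal block of Table 1 puts variables fixed at birth, such as gestation and birthweight, beside oxygen dependence at 28 days, at 36 weeks ("Oxygen dependence at 36 weeks of post menstrual age (yes/no") and at discharge. Postnatal steroids are recorded as yes/no with the number of courses, without dates. The follow-up block of the same table holds adult smoking, cotinine, weight and height. The Introduction says of the exposure: "Corticosteroids are administered to prematurely born infants to facilitate early extubation and reduce the incidence of BPD".

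**The concern.** With a non-randomised exposure, the covariate set decides what the exposure coefficient means. A variable confounds through its relation to both exposure and outcome. Whether it differs visibly in one sample of about 150 is a poor test of that, so the rule can go wrong in two ways.

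- **Omission.** A real confounder with a small observed difference is left out, and its share of the group difference stays in the steroid estimate.
- **Admission.** A variable affected by the exposure may well differ between groups and so be selected. Adjusting for it removes part of the steroid effect. It can also open a path through unmeasured severity that affects both that variable and lung function.

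The rule covers all outcome analyses, so admission could also reach the ventilation comparison. Ventilation mode was assigned from birth; postnatal steroids and later oxygen dependence come after it. Adjusting for them would weaken the protection that randomisation gives.

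At stake is the interpretation of the primary estimate, which the Introduction links to a review of steroid prescribing.

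**Working it through.** **The plan's own figures.** The protocol gives no figure for the effect of its adjustment rule, so there is none to reproduce here. Two figures are borrowed from the Sample size section: the target difference of 0.33 z and the 64 per group. The 64 serves only as a planned group size. It does not follow from its stated inputs: 2 × (1.960 + 1.282)² × 1.21² / 0.33² gives 283 per group. That is a separate matter and does not bear on this point.

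**Omission: assumed inputs.** None of these is in the documents: imbalance judged at two-sided p<0.05; a 1:1 split; a true standardised imbalance of 0.35 SD; an outcome shift of 0.3–0.5 z per SD of the confounder.

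1. Standard error of the observed standardised difference: √(1/64 + 1/64) = 0.177.
2. Selection threshold: 1.96 × 0.177 = 0.346 SD.
3. Probability of a miss: Φ((0.346 − 0.35)/0.177) = Φ(−0.02) ≈ 0.49. The noncentral t calculation gives 0.50 flagged at 64/64, 0.50 at 45/105 and 0.45 at 37/113.
4. Mean observed imbalance given a miss (truncated normal; the lower tail is negligible): 0.35 − 0.177 × φ(−0.02)/Φ(−0.02) = 0.35 − 0.177 × 0.399/0.492 ≈ 0.21 SD.
5. Bias when missed: 0.21 × 0.3 to 0.21 × 0.5 ≈ 0.06 to 0.10 z, or 19% to 31% of 0.33 (from unrounded 0.062 and 0.103).
6. Average bias under the rule: 0.49 × (0.06 to 0.10) ≈ 0.03 to 0.05 z, or 9% to 15% of 0.33.

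Step 4 is needed because a confounder is dropped only in samples where its observed imbalance is small, and the bias in those samples follows the observed imbalance.

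A simulation agrees (75 per group, 2,000 runs, true imbalance 0.3, slope 0.3, no steroid effect on oxygen dependence, true effect −0.33). A fixed set gave −0.34. The rule limited to the pre-exposure confounder gave −0.38, a gap of about 0.04 z.

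**Admission: what the text allows.** Three statements together leave it open: the undefined word "baseline", a neonatal sheet that mixes early and late items, and an Introduction that makes BPD something steroids are meant to change. The same simulation shows only that the direction is not fixed. It assumes a shift of ±0.6 on the latent scale for oxygen dependence and −0.5 z for oxygen dependence on lung function:

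| Assumed steroid effect on oxygen dependence | True total effect | Fixed pre-exposure set | Rule, pre-exposure confounder only | Rule, oxygen dependence also eligible |
|---|---|---|---|---|
| Lowers it | −0.23 | −0.23 | −0.26 | −0.35 |
| Raises it | −0.44 | −0.44 | −0.48 | −0.34 |

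Oxygen dependence was selected in 57% and 91% of runs respectively. The gap between the last column and the truth combines both faults. Every effect in the table is assumed, so it is not an estimate for this cohort.

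**The case against.** The strongest reply is that the protocol nowhere says oxygen dependence will be adjusted for. Table 1 is a data collection sheet, not a covariate list: it also contains the exposure and the ventilation arm. If "baseline" means pre-exposure, admission disappears. That stands. A reader might infer that the plan will adjust for post-exposure variables, or that the randomised comparison has lost its protection. The text supports only that such adjustment is permitted, and an unadjusted ventilation comparison will be shown as well.

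A second reply is that covariate lists and imbalance criteria belong in a full protocol or analysis plan. That is true of the list. But the article does state a selection rule, and a plan that follows it inherits the omission fault however "baseline" is defined.

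Third, the size is easily overstated. Multiplying the true imbalance by the slope (0.35 × 0.3 to 0.5 = 0.10 to 0.18 z) is tempting, but it ignores that a missed confounder has a smaller observed imbalance. The lower figures above are the right ones.

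Fourth, timing. The Introduction gives the purpose of steroids, not when they were given. Oxygen dependence at 28 days may precede exposure and mark the severity that prompted treatment. Excluding it outright could leave confounding by indication, so a blanket exclusion is not supported.

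Finally, the plan has safeguards: unadjusted estimates and propensity score matching. They help, but unadjusted estimates stay confounded and the matching is only a sensitivity analysis. One cannot say that it repeats the fault, because its variables are not named in the article.

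**Conclusion.** The concern holds in two parts of different strength.

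The omission fault follows from the stated rule and does not depend on what "baseline" means. Its size is illustrative: about 0.06–0.10 z when a confounder is missed and 0.03–0.05 z on average. It rests on the assumed p<0.05 criterion, 64 per group, one confounder with a 0.35 SD imbalance, and 0.3–0.5 z per SD.

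The admission fault is a possibility the wording leaves open, for the steroid contrast and for the randomised ventilation contrast. It can bias either estimate; the documents determine neither direction nor size. That oxygen dependence at 36 weeks and at discharge follows exposure is likely from the stated purpose of treatment, but no dates on the sheet show it.

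The rule should be replaced, because it governs the primary estimate and a better one needs only variables already collected.

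**What to change.** Replace the imbalance rule with covariate sets fixed before the data are examined.

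- **Steroid contrast.** Include gestation, birthweight z-score, sex, multiple birth, antenatal steroids, maternal smoking, surfactant and randomised ventilation arm, whatever the observed balance.
- **Keep out of the primary model and the propensity score.** Oxygen dependence at 36 weeks and at discharge, and variables measured at 24–28 years.
- **Oxygen dependence at 28 days.** Use it only where steroid timing shows that it came before exposure; otherwise confine it to a labelled sensitivity analysis. The fixed set holds no other marker of postnatal respiratory severity, so residual confounding by indication should be acknowledged.
- **Ventilation contrast.** Adjust for pre-randomisation variables only, and analyse by randomised arm.

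Keep the promised unadjusted estimates beside the adjusted ones. The cost is a change of wording and a few degrees of freedom for covariates that turn out to be balanced. Using the 28-day variable beyond a sensitivity analysis would also need steroid dates, which Table 1 does not record.

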### Eligibility criteria

Inclusion criteria are as follows:Young people who are now 24–28 years old who were born prematurely (below 29 weeks of gestation) and recruited into the UKOS study and term born controls.

Exclusion criteriaParticipants who are pregnant.

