### Sample size

The generally accepted lung function threshold for developing symptoms in COPD is a FEV_1_/FVC ratio below 70% of the predicted value^42^ which corresponds to a z-score of −2.19. The dexamethasone exposed group of the UKOS cohort had an FEV_1_/FVC ratio z-score of −1.83 which is above the threshold, but very close to it.^11^ In contrast the corticosteroid unexposed group had an FEV_1_/FVC ratio z-score of −0.89. The cohort was assessed at 16–19 years of age and are now ~8 years older and possibly symptomatic. Calculations have been based on the FEV_1_/FVC ratio, as it has been associated with a clinical symptom threshold.^43^ To detect a clinically significant difference in FEV_1_/FVC of 0.33 between the steroid and non steroid exposed (the difference in the mean FEV_1_/FVC z-score between the results of the 11–14 year olds and 16–19 year olds in the UKOS cohort) with a SD of the FEV_1_/FVC z-score of 1.21 and with 90% power and 5% significance, we will need 64 patients per group—128 in total. We will aim to recruit 150 patients from the UKOS cohort to allow for drop out.

To detect a clinically significant difference in the mean PAP of 2.31 mmHg as previously observed between children born preterm versus children born at term when they were 11–14 years of age with a SD of the mean PAP of 2.8 mmHg^16^ and with 90% power and 0.01 significance, we will need 44 patients per group (44 controls and 44 prematurely born young people). We will aim to recruit 50 term-born controls to allow for drop out.

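### The adjust-for-every-imbalance rule has no exception for the preterm–term comparisons, so the adjusted estimate there can condition on gestation and its consequences

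*Protocol article*

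**What the plan says.** All references are to the protocol article.

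- **Statistical analysis** gives one adjustment rule: "All study outcome analyses will be adjusted for observed baseline imbalances between groups", with each such factor entered as a fixed effect. Observed imbalance is the trigger, and no comparison is exempted. The same section promises both unadjusted and adjusted estimates with 95% confidence intervals, and places propensity score matching among the sensitivity analyses.
- **Outcome measures** makes spirometry, maximum VO2 and "PAP estimation by cardiac ultrasound of UKOS participants compared to term born controls" the secondary outcomes, so the rule covers them. The second hypothesis, on exercise capacity, uses the same contrast.
- **Eligibility criteria** defines the two groups by gestation: "born prematurely (below 29 weeks of gestation) and recruited into the UKOS study and term born controls".
- **Table 1**, neonatal part, collects gestation, birthweight, multiple birth, surfactant, mode of ventilation, postnatal glucocorticoids and oxygen dependence at three time points. Antenatal steroids are in the maternal part.
- **Sample size** sets the control group from a difference in mean PAP of 2.31 mmHg with SD 2.8 mmHg: "with 90% power and 0.01 significance, we will need 44 patients per group".

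**The concern.** In the preterm–term contrast, gestation is the exposure. Birthweight, surfactant, ventilation, neonatal steroids and oxygen dependence are largely its consequences. All of them will be found unbalanced, because the groups were chosen that way. A rule that enters every unbalanced factor as a fixed effect would therefore put them in the model beside the preterm/term indicator.

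Two things follow. First, the group coefficient no longer measures the difference that the secondary outcomes ask about, because part or all of it is carried by the added covariates. Second, gestation does not overlap between the groups (below 29 weeks against term), so the coefficient rests on extrapolating a fitted slope across the gap, and its standard error grows accordingly.

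Readers could then see a clear unadjusted difference beside a null adjusted one, with no prespecified basis for choosing between them.

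**Working it through.** **1. Reproduce the stated PAP sample size.** Inputs from the Sample size section: δ = 2.31, SD = 2.8, α = 0.01 (taken as two-sided), power 90%.

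n per group = 2 × [SD × (z₀.₉₉₅ + z₀.₉₀) / δ]² = 2 × [2.8 × (2.576 + 1.282) / 2.31]² = 43.7, rounded up to 44.

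This matches the protocol. Power at 44 per group is 90.2% by the normal approximation and 88.9% by the noncentral t. It is a plain comparison of two means with no covariates.

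**2. Cost of adding covariates.** If R² is the share of variation in the group indicator explained by the added covariates, the variance of the group contrast is multiplied by VIF = 1/(1 − R²). The residual SD is held at 2.8. Power for 2.31 mmHg at α = 0.01:

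| R² | VIF | 44 vs 44 | 128 vs 44 |
|---|---|---|---|
| 0 | 1.0 | 90% | 98% |
| 0.10 | 1.1 | 86% | 97% |
| 0.25 | 1.3 | 78% | 94% |
| 0.50 | 2.0 | 56% | 78% |
| 0.75 | 4.0 | 26% | 42% |
| 0.90 | 10 | 9% | 14% |
| 0.95 | 20 | 4% | 6% |

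The group sizes 128 and 44 are the Sample size section's requirements before the dropout allowance.

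**3. R² when gestation is entered.** Let p be the proportion of term participants, D the difference in mean gestation and s the within-group SD. Then R² = p(1 − p)D² / [p(1 − p)D² + s²], so VIF = 1 + p(1 − p)D²/s².

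The Introduction gives a mean gestation of 27 weeks for the UKOS adolescents studied at 11–14 years. The documents give neither the SD nor the controls' gestation. The assumed ranges are preterm mean 26.5–27 weeks, term mean 39–40 weeks (D = 12 to 13) and s = 1.0 to 2.0.

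- 128 vs 44, p(1 − p) = 0.190. Mildest case (D = 12, s = 2): VIF = 1 + 0.190 × 144/4 = 7.9, power 19%. Severest case (D = 13, s = 1): VIF = 1 + 0.190 × 169/1 = 33.2, power 4%.
- 44 vs 44, p(1 − p) = 0.25. VIF runs from 10.0 to 43.3, and power from 9% down to 2%.

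At the full recruitment target of 150 vs 50, with gestation 27 (SD 1.4) against 39.5 (SD 1.2):

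- Within-group variance = 0.75 × 1.4² + 0.25 × 1.2² = 1.83.
- R² = 0.1875 × 12.5² / (0.1875 × 12.5² + 1.83) = 0.941, so VIF = 17.0 and the standard error is multiplied by 4.12.
- Noncentrality falls from 2.31 / [2.8 × √(1/150 + 1/50)] = 5.05 to about 1.22, and power from 99% to about 9%.

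**4. What happens to the estimate.** This was simulated with 2,000 runs, 44 per group, and gestation about 27 (SD 1.3) against 39.8 (SD 1.2). The standard error of the group contrast rises from 0.60 to 3.3 mmHg.

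- If PAP falls linearly with gestation, the unadjusted difference is about 2.3 mmHg. The adjusted difference is about 0.02 mmHg, with a rejection rate of about 1%, which is the nominal level.
- If the effect is a step between preterm and term, the adjusted estimate stays near 2.3 mmHg, but power is about 3%.
- The unadjusted analysis keeps 88–89% power in both cases.

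**The case against.** **The power survives in the unadjusted analysis.** A reader might infer that the study loses its PAP power. It does not. The unadjusted estimate is also to be presented, and that is the analysis the sample size was built for. This stands, and it limits the loss to the adjusted analysis. What remains is that the text says analyses will be adjusted and presents the unadjusted ones to show what adjustment does. It never says which leads for this comparison.

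**Gestation is not named as a covariate.** Table 1 is a data collection sheet. Read too literally, the rule would also adjust the steroid comparison for steroid exposure, so an ordinary reader would leave out the variable that defines the groups. A covariate list may also sit in an analysis plan that is not shown. This has weight for gestation itself and makes the figures above conditional. It does not cover birthweight, surfactant or oxygen dependence, which do not define the groups but are unbalanced by design. A plan that left these out would depart from a rule stated for all outcome analyses.

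**Matching of term controls is an inference.** A reader might conclude that propensity matching will fail for want of overlap. The article describes matching as a sensitivity analysis used in the earlier UKOS follow-up. It does not say that term controls will be matched to preterm participants. Likewise, "Neonatal baseline data will be compared for the children recruited and not recruited at age 24–28 years" concerns UKOS members, so it shows only that the authors call neonatal data baseline.

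**The adjusted estimate is not always meaningless.** Under a step effect it stays centred near the true difference, though far too imprecise to use. Covariates weakly related to group (R² up to about 0.1) cost only about 4 points of power at 44 vs 44, and about 1 point at 128 vs 44.

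**Conclusion.** The point holds in a limited form. As written, the rule reaches the secondary preterm–term comparisons. There it admits gestation and the consequences of prematurity as adjustment factors, which may remove the effect being studied.

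If gestation enters, VIF is about 8–43 over the two allocations examined, and adjusted PAP power is about 4–19% at 128 vs 44. These figures rest on assumed gestation SDs and an assumed control mean, a linear model with a common slope, and a residual SD unchanged at 2.8 mmHg. No equivalent figure can be given for birthweight or the neonatal treatments, because the documents do not give their distributions. The R² table shows what they would cost at a given strength of association.

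The documents do not support the stronger reading that the PAP comparison as a whole is underpowered. The 44 per group is correct and applies to the unadjusted estimate. The primary comparison, steroid exposure within the preterm group, is outside this point.

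**What to change.** 1. Confine the imbalance-adjustment rule to the comparisons within UKOS (steroid exposure and mode of ventilation).
2. For the main preterm–term comparisons, adjust only for prespecified factors that are not consequences of prematurity, for example age, sex, race and maternal smoking.
3. State that gestation, birthweight, surfactant, ventilation, antenatal and postnatal steroids and oxygen dependence are neither adjusted for nor matched on in those comparisons.
4. Name the leading estimate, unadjusted or adjusted for the short list.
5. Keep the second hypothesis's question, whether lung function, cardiac function and exercise habits explain the exercise deficit, as a separate and labelled explanatory (mediation) analysis. Treat adult smoking or cotinine as a sensitivity analysis.

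The cost is a few sentences in the Statistical analysis section, with no new data and no change to the sample size. It should be settled before the groups are compared, so that the covariates are not chosen from the observed imbalances.

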Lung volumes will be assessed by means of measurements of functional residual capacity with the use of a helium-dilution technique (FRC_He_) and FVC by means of spirometry.^29^The following assessments of lung volumes will also be undertaken: functional residual capacity as assessed by means of plethysmography (FRC_pleth_) and plethysmographic assessments of total lung capacity and residual volume. Two measurements within 5% of each other will be averaged to calculate the results.^29^

The diffusing capacity of the lung for carbon monoxide (DL_CO_), alveolar volume, and gas transfer per unit volume will be assessed with the use of the single-breath gas-transfer technique.^30,31^

The fraction of exhaled nitric oxide (Fe_NO_) will be measured by means of a real-time method with the use of a computerised system and visual display. As a measure of respiratory muscle function, we will measure the maximum inspiratory and expiratory pressures using a respiratory pressure metre.

All lung-function results will be reported using established reference ranges and will be converted into z scores as appropriate.^32–37^

Participants will perform a cardiopulmonary exercise test (CPET) on a cycle ergometer to determine the maximum oxygen uptake (VO_2_) as a measure of maximum exercise capacity (Table 3). In addition, they will undergo a shuttle sprint test so that the results can be compared with those obtained when the participants were 16 to 19 years.^19^

**Table 3 Tab3:** Cardiopulmonary exercise test data collection sheet

Cardiopulmonary exercise testing parameters
Peak V̇O_2_ Absolute (mL/min)
Peak V̇O_2_ Specific (mL/kg/min)
Peak V̇O_2_ (%Pred)
Peak HR (bpm)
Peak HR (%pred)
V̇E/V̇CO_2_ Slope
Peak O_2_ pulse (%pred)
Peak O_2_ pulse (V̇O_2_/HR)
Sat. O_2_ Pre
Sat. O_2_ Post
Peak V̇E (L/min)
BR (L)
BR (%)

*BPM* beats per minute, *BR* Breathing reserve, *HR* heart rate, *L* litre, *mL/kg/min* millilitre per kilogram per minute, *V̇O*_2_ Maximum rate of oxygen consumption, *Sat* Saturation, *V̇CO*_2_ maximum rate of carbon dioxide production, *V̇E* minute ventilation, *%Pred* percentage predicted.

Doppler echocardiographic studies will be undertaken to assess cardiac structure, function, PAP and diagnose PH^38^ (Table 4).

**Table 4 Tab4:** Echocardiography data collection sheet

Echocardiographic measurements
TR peak velocity (m/s)
PA diameter (mm)
RVOT acceleration (time,m/s)
IVC diameter (mm)
Estimated RAP (mmHg)
SPAP (mmHg)
MPAP (mmHg)
RA area (cm^2^)

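### Selective follow-up is checked and corrected with neonatal data only, although the cohort's own adolescent lung function is available and is likely to be more informative

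*Protocol article*

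**What the plan says.** The Statistical analysis section of the protocol article deals separately with people who are not seen and with tests that are not done.

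- **Not seen.** "Neonatal baseline data will be compared for the children recruited and not recruited at age 24–28 years", in order to judge how representative the group is. Then: "Those variables that differ between recruited versus not recruited will be further adjusted for a sensitivity analysis".
- **Not done.** "Some participants will be unable to complete all tests and, so, multiple imputation using chained equations will be used to impute missing data". The variables in the imputation model are not listed.

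Other sections show what else is held on the cohort. The Introduction links steroid exposure to "impaired lung function at 11–14 years^10^ and 16–19 years.^11". The Sample size section gives values from the 16–19 wave: "The dexamethasone exposed group of the UKOS cohort had an FEV_1_/FVC ratio z-score of −1.83" and "In contrast the corticosteroid unexposed group had an FEV_1_/FVC ratio z-score of −0.89". The Assessment section includes the shuttle sprint test "so that the results can be compared with those obtained when the participants were 16 to 19 years".

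**The concern.** The article names the data for the representativeness check, and they are neonatal only. The question is whether the adults who attend resemble those who do not in respiratory health. The most direct evidence on that is the same outcome measured in the same people 8 or more years earlier. Neonatal variables remove selection bias only as far as they explain who attends, and without the adolescent values nobody can see whether they do.

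Selection is plausible. Under Recruitment, participation depends on a reply to an email or a telephone contact. Under Setting, all testing is at one hospital. The exposure groups already differed by 0.94 z at 16–19 years, so if lung function affects attendance, attendance may differ by exposure.

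At stake are the preterm group means, which feed the comparison with term controls, and the exposed–unexposed contrast, which is the primary analysis. The reason given for missing tests raises a related issue. Inability may depend on the value that would have been seen, whereas chained equations in their standard form assume that observed data explain the missingness.

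**Working it through.** **The plan's own figures.** The article gives no rate of non-attendance or missing tests, so there is none to reproduce on this point. Its planned difference (0.33) and SD (1.21) serve below only as a scale. The 64 per group derived from them does not reproduce: 2 × (1.96 + 1.2816)² × (1.21/0.33)² = 282.5, or 283 per group (two-sided 5%, 90% power). That is a separate matter, and nothing here rests on it.

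**Inputs from the documents.** Mean FEV1/FVC z-score at 16–19 years is −1.83 (exposed) and −0.89 (unexposed), a gap of 0.94. SD is 1.21. The recruitment target is 150. The Introduction mentions 193 cohort members studied at 11–14 years. If those 193 were the pool and 150 attended, (193 − 150)/193 = 43/193 = 22% would not be seen. The number to be invited is not stated, so this is only an illustration.

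**Assumptions.** Adult group means equal the adolescent means. The adolescent–adult correlation ρ is 0.5, 0.7 or 0.85. The missing share is 5%, 15%, 30% or 50%. The odds of being missing double for each SD (1.21 z) of lower lung function. Neonatal predictors were not simulated; any predictive value they have would shrink the bias.

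**Model** (1,000,000 simulated people per group):
- adolescent value = group mean + 1.21·u
- adult value = group mean + 1.21·(ρ·u + √(1 − ρ²)·e)
- P(missing) = 1/(1 + exp(−(c − (ln 2/1.21)·x))), where x is the adolescent or the adult value and c is set to give the overall missing share
- bias of a mean = mean among those observed − true mean
- bias of the gap = exposed bias − unexposed bias; a positive value means the gap looks too small

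**Same mechanism in both groups, ρ = 0.7 (z units):**

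| Missing | Driven by | Exposed mean | Unexposed mean | Gap | Gap once adolescent value is used |
|---|---|---|---|---|---|
| 5% | adolescent | +0.036 | +0.021 | +0.015 | +0.001 |
| 5% | adult | +0.051 | +0.033 | +0.019 | +0.009 |
| 15% | adolescent | +0.098 | +0.067 | +0.031 | −0.002 |
| 15% | adult | +0.141 | +0.093 | +0.048 | +0.025 |
| 30% | adolescent | +0.187 | +0.135 | +0.052 | 0.000 |
| 30% | adult | +0.269 | +0.195 | +0.074 | +0.039 |

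Over all correlations and 5–50% missing, the gap bias runs from 0.008 to 0.091. The last column uses a within-group regression on the adolescent value. Participation weights built on that value need the same assumption, but were not simulated.

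**Selection acting in one group only, ρ = 0.7:**
- 15% missing: +0.083 (adolescent-driven) to +0.118 (adult-driven) if in the exposed; −0.084 to −0.120 if in the unexposed.
- 30% missing: +0.161 to +0.229, or −0.164 to −0.228.

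If selection acts in both groups with the same 15% share in each, the gap bias is 0.000 to 0.004.

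**Scale.** 0.12/0.33 = 36% of the planned difference, but 0.12/0.94 = 13% of the gap seen at 16–19 years. With 75 per group (assuming an equal split of 150), the standard error of the difference is 1.21 × √(2/75) = 0.198. A shift of 0.03–0.05 is then about a quarter of a standard error or less, and 0.12 about 0.6 of one.

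**Why the earlier value should not simply join the outcome model.** It lies after steroid exposure and on the path to adult function. Under the assumptions above, the within-group slope of adult on adolescent value equals ρ, so the adjusted gap is 0.94 × (1 − ρ): 0.47, 0.28 or 0.14 for ρ = 0.5, 0.7 or 0.85. Most of what the study sets out to estimate could be adjusted away.

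**The case against.** The strongest defence is that neonatal variables are a safe choice for the procedure as written. Because that procedure adds covariates to the outcome model, restricting it to variables that precede or accompany the exposure avoids conditioning on a consequence of it. That is correct, and it is why the remedy has to be weighting. It does not explain why the descriptive comparison of recruited and non-recruited members leaves the adolescent values out.

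Three stronger readings are tempting, and the documents do not support them.

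- *The imputation ignores adolescent lung function.* No predictors are listed, so nothing shows these values are excluded. Predictor lists and analyses for data missing not at random are commonly left to the full protocol or SAP, and their absence from an article is no fault.
- *The plan understates impairment.* No passage says that inability or non-attendance is commoner in the exposed or in those with worse lungs, and healthier people may also stay away. A simple sum with 15% of exposed and 5% of unexposed missing, each truly 1 SD worse than imputed, gives (0.15 − 0.05) × 1.21 = 0.12 z of shrinkage. Swapping the two assumed rates gives 0.12 z the other way.
- *Inability threatens the primary outcome.* The battery includes cycle ergometry, a shuttle sprint and bronchial challenge. Inability is likelier to affect these than basic spirometry, though the article gives no rates.

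Two limits also stand. The article does not say that earlier measurements exist for every non-recruited member. Term controls come from local advertising with no earlier waves described, so the preterm–term comparisons would be helped on one side only.

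**Conclusion.** The point holds for selective follow-up: the stated check and correction use neonatal data only, while the cohort holds earlier measurements of the primary outcome itself. The consequence is possible bias, not demonstrated bias. If worse lungs make attendance less likely, preterm means look too good, by 0.07–0.14 z at an assumed 15% missing and correlation 0.7. The exposed–unexposed contrast then moves by about 0.03–0.05 z if one mechanism acts in both groups, and by up to about 0.12 z in either direction if it acts in one group only; with 30% missing these figures are larger. The direction for the contrast is unknown. All sizes rest on assumed rates, and neonatal adjustment would reduce them by an unknown amount.

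Using the adolescent values removes the bias if attendance depends on them, and only about halves it (at correlation 0.7) if attendance depends on current function. For imputation, the documents support a request for confirmation and no more. This is a worthwhile, inexpensive improvement to a stated method, and it does not overturn the primary analysis.

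**What to change.** 1. Extend the recruited versus not-recruited comparison to the FEV1/FVC z-scores at 11–14 and 16–19 years and the shuttle distance at 16–19, where available, by exposure group. Report how many people have each.
2. Run the selection sensitivity analysis with inverse-probability-of-participation weights that include these values alongside the neonatal variables and steroid exposure. Do not add the adolescent values to the outcome model.
3. Confirm that the same values are in the imputation model for the preterm group.
4. Because inability is the stated reason for missing tests, add a delta-shifted sensitivity analysis for the exercise outcomes, for example lowering imputed values by 0.5 and 1 SD. Recording why a test was not done would let the shift apply only to inability.

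Items 1 to 3 use data from earlier waves. The cost is some extra analysis and slightly wider intervals from weighting. Recording reasons needs one form field, which has to be in place before assessments finish. Term controls do not benefit from items 1 to 3.
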